### Outcomes

#### Effect Measures

The effects of the intervention will be assessed on the level of the patient. The primary outcome of the study is the sick leave duration until full sustainable RTW, defined as the duration of the sick leave in calendar days from the day of surgery until full RTW, in their own work or other work with equal earnings, for at least 4 weeks without (partial or full) recurrence [44]. The recurrence of sick leave due to the gynecologic surgery within the four week period after initial full RTW will be added to the preceding period of the sick leave. The RTW will be assessed by a monthly electronic sick leave calendar.

Secondary outcomes that will be assessed are:

Recovery, measured by the Recovery Index-10 (RI-10) a validated recovery-specific questionnaire [45];Self-reported quality of life, assessed by the Dutch versions of the EuroQol-5D (EQ-5D) [46] and the Short-Form Health Survey (SF-36) [47,48];Duration of sick leave until first RTW, and total duration of sick leave due to the gynecological surgery for the entire follow-up period, both measured by the monthly sick leave calendars;Self-efficacy, assessed by the Dutch adaptation of the General Self-Efficacy Scale (GSES) [49];Coping, assessed by the Pearlin Mastery Scale (PMS) [50];Pain intensity, measured by the Von Korff questionnaire (VAS) [51]; and(Post) operative complications both assessed through self-report and by the review of surgical reports. Complications include: (1) enlargement of the wound (≥ 8cm), (2) unintended injury to other structures (eg, bowel, bladder, ureter), (3) unexpected blood loss requiring transfusion, (4) prolonged hospital stay, (5) readmission within 72 hours (overnight), (6) repeat surgery within 2 weeks, and (7) postoperative infection requiring antibiotics.

#### Prognostic Factors

Before surgery, data about potential prognostic factors will be collected. In case of coincidental and meaningful differences, analyses will be adjusted for the following characteristics: (1) sociodemographic data such as age, education level, and ethnicity; (2) personal factors such as expectation, motivation, and intention toward RTW, duration of sick leave in the past 3 months; and (3) work related factors such as physical workload and potential work related psychosocial factors, assessed by the Dutch Musculoskeletal Questionnaire (DMQ) [52] and the Job Content Questionnaire (JCQ) [53].

In case of an unequal distribution of severe complications (defined as: wound enlargement with more than 8cm or repeat surgery within 2 weeks), between the two study arms, the analyses will be adjusted for these surgery-related characteristics as well.

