### Randomization

The randomization takes place at the level of the clusters and determines the order in which the intervention program is implemented in the participating hospitals. The randomization will be performed by a statistician using a computer generated list of random numbers.

The patients are informed about the allocation of treatment by the research team after the patient’s informed consent and the completion of the first questionnaire before surgery. As the treatment allocation depends on the scheduled date of the surgery, and the implementation phase of the hospital in which they are being operated, it is predetermined for each participant, potentially causing selection bias. To minimize the risk of selection bias, the participants will not be informed about the study design, and will be counseled as if they have equal chances between receiving the usual care or the intervention program. For this reason, counseling will be done by the research team, rather than by their own physician, who might be, for example, more willing to include patients during the intervention phase than during the control phase. Moreover, physicians will be blinded to the randomization schedule, and will only be informed about the start of the intervention phase approximately one month before the actual implementation. Once the intervention phase has started, the importance of not communicating this information with the potential patients will be emphasized.

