##### eHealth Intervention

The patient webportal (Figure 3, [39] aims at empowering its users and improving communication between patients and their employers, as well as improving the communication between the involved health care professionals during the perioperative period. Access to the webportal will be given to the patients approximately 2 to 4 weeks prior to surgery by the research team, by providing a username and temporary password. The instructions are given by email, and it is explained that if patients require assistance, they can contact the research team by phone or email. If patients fail to log in, an automatic reminder is sent to them one week before their surgery to remind them about the webportal and its functionalities. User authentication will make it possible to analyze website activity for each individual participant (visit duration, number of sessions, number and details of pages visited).

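### Adjusting the effect analyses for severe complications when the arms differ can remove part of the program's effect from the adjusted return-to-work hazard ratio

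*Protocol article*

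**What the plan says.** The Prognostic Factors section first covers characteristics collected before surgery, which become covariates if coincidental and meaningful differences appear. It then adds a second rule for when the arms differ on certain events: "In case of an unequal distribution of severe complications (defined as: wound enlargement with more than 8cm or repeat surgery within 2 weeks"). For that case it says that "the analyses will be adjusted for these surgery-related characteristics as well". This second rule is not limited to coincidental differences and gives no threshold for unequal.

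The Effect Measures section lists complications as a secondary outcome, with "operative complications both assessed through self-report and by the review of surgical reports". Wound enlargement (there at least 8 cm) is item 1 of that outcome, and repeat surgery within 2 weeks is item 6. Table 3 likewise shows complications both among the secondary outcomes and among the prognostic factors.

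On timing, the Randomization section says: "The randomization takes place at the level of the clusters and determines the order in which the intervention program is implemented". A patient's arm therefore follows from her hospital and her scheduled surgery date. The eHealth Intervention section says: "Access to the webportal will be given to the patients approximately 2 to 4 weeks prior to surgery by the research team".

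The Effect Evaluation section promises intention-to-treat analyses and both a crude and an adjusted Cox model. The adjusted model lists hospital, type of surgery performed, time period and an optional period-by-intervention interaction. Complications are not on that list.

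**The concern.** A baseline covariate cannot be affected by treatment, so adjusting for it leaves the treatment effect intact. These complications are not baseline covariates. They follow allocation and the start of the program, and the plan itself counts them as an outcome. If the program changes their frequency, part of its effect on return to work runs through them, and a model that holds them fixed no longer estimates the whole effect.

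The trigger adds to the problem, because the covariate enters only when the arms differ. Such a difference may be chance, case mix, calendar period or the program, and the rule treats all four alike. If the program raised complications, the resulting delay in return to work would be taken out of the adjusted hazard ratio. If it lowered them, that gain would be taken out. The choice of model would also depend on an observed outcome.

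**Working it through.** **Order of events.** (1) Roll-out order is randomised. (2) Hospital and surgery date fix the patient's arm. (3) Portal access opens 2 to 4 weeks before surgery. (4) Surgery takes place, when the wound may be enlarged. (5) Repeat surgery may occur within 2 weeks. (6) Return to work is counted from the day of surgery. The rule conditions on steps 4 and 5.

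**Can the program affect them?** For repeat surgery the article describes routes. Patients are instructed to follow the approved plan, for which approval is asked on the first postoperative day. A recovery monitor at days 2, 4, 7 and 14 sends patients who fall behind to a health professional. The program could cause, prevent or bring forward the detection of such events. For wound enlargement during the operation, no route is described.

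**Size.** The article states no figure for this point: neither complication rates nor the effect of a complication on return to work. The following are assumptions: p0 and p1, the complication probabilities in control and intervention; c, the hazard ratio for return to work after a complication; d, the direct hazard ratio of the program.

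At the start of follow-up the hazard ratio without the complication covariate is

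d × [(1 − p1) + p1·c] / [(1 − p0) + p0·c].

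With d = 1.0, p0 = 0.05, p1 = 0.15 and c = 0.4: (0.85 + 0.06) / (0.95 + 0.02) = 0.91 / 0.97 = 0.94. Women with a complication stay off work longer and form a growing share of those still at risk, so the Cox average over follow-up is lower, at 0.90 in simulation. A model containing the complication covariate targets d itself, here 1.00.

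Simulated Cox models (exponential times, control median 60 or 65 days, censoring at 365 days) gave:

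| p0 vs p1 | c | d | HR without covariate | HR with covariate | Shift |
|---|---|---|---|---|---|
| 5% vs 15% | 0.4 | 1.5 | 1.29 | 1.50 | 0.21 |
| 5% vs 10% | 0.4 | 1.5 | 1.35 | 1.46 | 0.11 |
| 5% vs 10% | 0.3 | 1.5 | 1.33 | 1.49 | 0.16 |
| 5% vs 10% | 0.3 | 1.2 | 1.10 | 1.21 | 0.11 |
| 5% vs 15% | 0.4 | 1.0 | 0.90 | 1.00 | 0.10 |
| 5% vs 10% | 0.3 | 1.0 | 0.93 | 0.99 | 0.06 |
| 3% vs 5% | 0.5 | 1.2 | 1.17 | 1.20 | 0.03 |
| 2% vs 4% | 0.5 | 1.0 | 0.98 | 1.00 | 0.02 |
| 5% vs 5% | 0.3 | 1.2 | 1.18 | 1.20 | 0.02 |

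At 5% versus 7% with c = 0.5 the shift was about 0.01 to 0.04. Single estimates carry simulation error: with 20,000 patients the standard error of the log hazard ratio is about 2/√20,000 = 0.014, or about 0.02 at a hazard ratio of 1.5. That is why the adjusted values scatter around d.

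Three readings follow:
- The last row has no difference in complications but still shifts by 0.02. That part is non-collapsibility of the hazard ratio, not a lost program effect.
- With the direction reversed (10% control, 5% intervention, c = 0.4, d = 1.5), 1.577 became 1.535, so a benefit is trimmed.
- With an unmeasured factor driving both complications and return to work (d = 1.0, observed rates 7% versus 19%), 0.91 became 1.06. Adjustment then does more than remove a path; it adds bias.

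**Which estimate is exposed?** Hospital and time period enter only the adjusted Cox model. In a stepped wedge the share of patients on the intervention rises with calendar time, so the crude model leaves period effects in the comparison. The adjusted estimate is the one that respects the design, and it is the one the rule can change.

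**The case against.** The best case for the plan has four parts.

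- **Harm would not disappear.** Complications are a secondary outcome from two sources, and a crude Cox model is planned. This stands against any claim that harm would go unreported. It does not restore the consequence for return to work to the adjusted hazard ratio, and the crude model lacks hospital and period.
- **An imbalance need not come from the program.** With nine hospitals crossing over in sequence, chance, case mix and changes in surgical practice can all produce one. The plan's description of these events as surgery-related suggests that this is what the rule was meant to handle. This stands, especially for wound enlargement. It shows why the rule was written, but the rule applies equally when the program is the cause.
- **There is a safeguard.** The gynecologist can withhold approval of the convalescence plan after severe complications. That limits one route in those patients, but does not make repeat surgery a baseline variable.
- **The shift may be small.** With low rates, small differences and a moderate effect of a complication, it is a few hundredths. This stands, and the size is therefore given as a range.

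A reader might also infer that the covariate for type of surgery performed, the surgery subgroups and the economic evaluation share the defect. The article does not support this. It describes no route from the program to conversion during surgery, and it does not say whether the subgroups use scheduled or performed type. The Economic Evaluation section contains no complication adjustment.

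**Conclusion.** The rule is wrong as written. It conditions the effect analyses on post-allocation events that the plan itself counts as an outcome, and only when the arms differ on them. It also sits uneasily with the intention-to-treat commitment and with the covariate list under Effect Evaluation, which omits complications.

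The size cannot be fixed from the article. Under the assumptions shown, the adjusted hazard ratio moves by about 0.01 to 0.04 in mild settings and by about 0.06 to 0.2 at 5% versus 10-15% with a post-complication hazard ratio of 0.3 to 0.4. At the upper end a net harm of 0.90 would be reported as 1.00. These figures assume that the rate difference is caused by the program, which is plausible mainly for repeat surgery.

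A reader might go further and conclude that the plan hides harm. It does not: complications are still reported as an outcome. What is lost is their consequence for return to work in the adjusted estimate.

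**What to change.** Delete the sentence under Prognostic Factors that adjusts for severe complications. Keep complications out of the main intention-to-treat effect models, as the covariate list under Effect Evaluation already does. Report complications by arm as the secondary outcome they are. If a complication-adjusted model is wanted to explore chance or case-mix imbalance, present it as a labelled sensitivity analysis beside the main result. In Table 3, list complications only as an outcome.

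The cost is one deleted rule and a label. No data or patients are added, the sample size of 454 is unaffected, and the article states that data cleaning and analysis had not begun at submission. The price is that a chance imbalance in complications stays in the main estimate, where the confidence interval already allows for chance; the sensitivity analysis can show its influence.

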#### Cost Measures

The costs will be measured from a societal perspective and consist of: (1) costs of the intervention, (2) health care utilization, and (3) costs associated with lost productivity. All of the costs will be converted to the year 2014 using consumer price indices [54]. The discounting of costs will not be necessary because the follow-up period is limited to one year.

The intervention costs are those that are related to implementing and operating the new care program, and will be estimated using a bottom-up approach. The detailed information regarding the quantity and unit prices of the following resources will be collected: (1) training of involved health care professionals (clinical staff, OP, OT), (2) the eHealth intervention (hosting of webportal, administrator time), and (3) the occupational intervention (number and duration of consultations).

The health care utilization will be assessed on a monthly basis using a retrospective electronic questionnaire. Only the health care costs related to the gynecological surgery will be collected and include: (1) surgery and hospitalization; (2) visit is to health care professionals in primary or secondary care and visits to alternative medicine therapists; (3) medication; and (4) home care and informal help. If available, Dutch guideline prices will be used to value health care utilization. If cost guidelines are not available, costs will be estimated using real prices or population-based estimates if available in the literature. The prices of the Royal Dutch Society for Pharmacy will be used to value medication [55].

The costs associated with productivity loss consist of absenteeism and presenteeism costs. The absenteeism will be assessed by monthly sick leave calendars. The human capital approach will be used to calculate the costs of losses to production as a result of sick leave due to the gynecologic surgery (net number of days on sick leave during follow-up, multiplied by the estimated prices of production loss of a worker per day of sick leave). The presenteeism (reduced productivity while at work) will be assessed with two items of the Productivity and Disease Questionnaire [56]. A decline in the amount or quality of work performed due to the gynecologic surgery compared to the level at which the patient normally performs, will be considered as presenteeism. The costs associated with presenteeism will be calculated by multiplying the presenteeism score during follow-up by the estimated price of production loss per day.

#### Process Measures

A process evaluation will be conducted to evaluate the implementation process of the intervention [57]. The assessment of the extent to which the intervention program was applied as intended will provide valuable insight into the facilitators and barriers for future implementation. The process evaluation will take place both on the level of the cluster as well as the patient, and both quantitative and qualitative methods will be used. An automatically generated weblog will enable the analysis of the website activity for each individual participant, giving more insight into which patients used the eHealth intervention, and how it is being used. The appointment system and patient records of the OP will enable us to analyze the number of consultations that have taken place, as well as the reasons for cancellations, and the occurrence of any protocol deviations. By means of an Internet questionnaire at the end of the follow-up period, patient satisfaction, perceived effectiveness, and any usage barriers will be assessed. The principle investigator will continuously collect reasons for exclusion and dropout during the trial. In accordance to the prior process evaluation conducted [27], the following process measures are included: (1) reach, extent to which the intervention reaches the target population; (2) dose delivered, extent to which the intervention is delivered to the target population; (3) dose received, extent to which the participants used the intervention; (4) fidelity, extent to which the intervention was delivered as planned; and (5) attitudes, satisfaction, perceived effectiveness, and usage barriers.

### Cointerventions and Contamination

Cointerventions during the intervention period cannot always be avoided. However, we will be able to determine whether patients received cointerventions by means of the monthly cost diaries. The risk of contamination is reduced by the cluster design of the trial. To assess whether contamination occurred, the patients in both groups are asked about the instructions they received at discharge, which will then be compared to the convalescence recommendations implemented during the intervention phase of the study.

### Data Collection

The surgery is considered T_0_. The data will be collected by means of self-reported electronic questionnaires [58] before surgery and 2 weeks (T_1_), 6 weeks (T_2_), 12 weeks (T_3_), 26 weeks (T_4_), and 52 weeks (T_5_) after surgery. In addition, all of the participants will be requested to fill out a monthly electronic sick leave calendar and cost diary. The patients that are not sick listed, and do not have medical costs during 3 consecutive months, receive a shortened version of the monthly questionnaire. In the case of no response, the patients receive an electronic reminder after 1 and, if necessary, 2 weeks. Every 3 months an attempt will be made to complete missing data regarding RTW, sick leave, and health care usage per email, post, and/or telephone. Table 3 provides an overview of all outcome measures and assessment instruments used in this trial. Not all of the instruments have been validated for Internet use.

**Table 3 table3:** Assessment of study outcomes.

Outcome measures		–		+	+	+	+	+
		± 4 weeks	Surgery (T_0_)	2 weeks (T_1_)	6 weeks (T_2_)	3 months (T_3_)	6 months (T_4_)	12 months (T_5_)
**Primary**								
	Duration of sick leave until full sustainable RTW	Monthly sick leave calendar^a^						
**Secondary**								
	Duration of sick leave until first RTW	Monthly sick leave calendar^a^						
	Total duration of sick leave	Monthly sick leave calendar^a^						
	Recovery (RI-10)	x		x	x	x	x	x
	Quality of life (EQ-5D)	x		x	x	x	x	x
	Quality of life (SF-36)	x				x	x	x
	Self-efficacy (GSES)			x		x		x
	Coping (PMS)			x		x		x
	Pain intensity (VAS)			x	x	x	x	x
	(Post) operative complications			x	x			x^b^
**Prognostic factors**								
	Social demographic variables	x						
	Personal factors	x						
	Work related factors (DMQ, JCQ)	x						
	Type of surgery/complications		x					
**Cost**								
	Care program	Bottom-up approach^c^						
	Health care utilization	Monthly cost diary^a^						
	Productivity loss	Monthly sick leave calendar^a^						
**Process** ^d^								
	Compliance (dose received)	Continuously by weblog						
	Attitudes (satisfaction, perceived effectiveness, usage barriers)					x		x
	Satisfaction Patient Satisfaction with Occupational Health Services Questionnaire					x		x

^a^short version after 3 consecutive months without sick leave or health care usage

^b^review of surgical reports

^c^calculated by research team

^d^only intervention group

### Blinding

The participants, care providers, and researchers cannot be blinded for the allocated treatment. However, analysis of the data by the researcher will be blind, as all of the patients receive their own study code, under which their data is stored in the database. The assessment of the outcomes is measured through self-reported questionnaires.

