### Trial Design

This trial is designed as a cluster, randomized controlled, stepped wedge trial, which involves a sequential rollout of the intervention in the participating clusters over several time periods. In our study, clusters are the departments of obstetrics and gynecology in nine different hospitals in the Netherlands. Each time period (TP) takes 2 months. At the start of the trial (TP_1_), all of the patients scheduled for a surgery in all of the participating hospitals receive usual care (control phase). After two months (TP_2_), the intervention is implemented in the first cluster, and from now on the patients scheduled for a surgery in this hospital will receive the intervention program, while in all of the other hospitals the patients still receive usual care. The patients in cluster 2 who underwent surgery during TP_1_ remain in the control group until they finish the 12 month follow-up. During TP_3_, the intervention program continues in cluster 1, and the intervention is implemented in cluster 2 as well, resulting in the deliverance of the intervention program to the patients in clusters 1 and 2 that will undergo surgery from this point onward, while patients in clusters 3 to 9 serve as the control group. At the beginning of TP_4_, cluster 3 starts with the intervention, etc. This is repeated until the intervention is implemented in all clusters (TP_10_). Figure 1 illustrates the study design.

A cluster design was chosen to minimize the risk of contamination, as our intervention targets both health care providers and patients. A stepped wedge approach was employed because of the unique feature of an unidirectional crossover, preventing the intervention to be withdrawn from the hospital during the trial [34-36]. Because there is substantial evidence from our previous trial that the care program under study will be effective, this is particularly convenient, as hospitals will be able to keep using the intervention after the trial. Moreover, it enables us to study the implementation process carefully, giving valuable insight into barriers and facilitators for future broader implementation.

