### Statistical Analyses

#### Effect Evaluation

All further described analyses will be performed at the patient level, according to the intention-to-treat principle. In addition, for all tests, a two-tailed significance level of *P*≤.05 will be considered statistically significant. The statistical software packages that will be used include SPSS (version 16.0) and STATA (version 11.2).

The baseline characteristics will be summarized using descriptive statistics, and compared between the experimental and control group to verify prognostic comparability. In case of coincidental and meaningful differences, these variables will be used as covariates in the further described models.

For the primary outcome, the duration of sick leave until full sustainable RTW, Cox regression analyses will be used to investigate the intervention effect. Both the crude and adjusted analyses will be performed. In the adjusted analyses, the following variables will be used as covariates: (1) hospital, to adjust for clustering (random gamma effect); (2) type of surgery performed; (3) time period, to adjust for naturally occurring changes over time irrespective of the intervention; and (4) optionally, (time period) x (intervention) interaction term, to adjust for time effects (the longer the care program is implemented, the more effective it might be).

The differences in secondary outcomes will be assessed using generalized linear longitudinal mixed models. All of the available measurements (2 weeks, 6 weeks, 12 weeks, 26 weeks, and 52 weeks) will be used, and the baseline scores will be used as covariates, as well as the hospital and the type of surgery (random effect).

To assess whether protocol deviations caused bias, a per protocol analysis will be performed, and the results will be compared to the intention-to-treat analyses. In addition, several subgroup analyses will be performed. The predefined subgroups will be: (1) hysterectomy (TAH, VH, TLH); (2) minimally invasive hysterectomy (VH, TLH); (3) abdominal hysterectomy only; and (4) laparoscopic adnexal surgery only.

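### Study codes do not blind the analysis: in the adjusted primary Cox model, hospital and time period together reveal the arm, and no other masking step is described

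*Protocol article*

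**What the plan says.** The Blinding section of the protocol article first concedes that "The participants, care providers, and researchers cannot be blinded for the allocated treatment". It then says that "analysis of the data by the researcher will be blind, as all of the patients receive their own study code", under which the data are stored. The code is the only reason given. The article mentions no recoded arm labels, no independent analyst and no staged release of data.

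The Randomization section says that "the treatment allocation depends on the scheduled date of the surgery, and the implementation phase of the hospital in which they are being operated", and that "it is predetermined for each participant, potentially causing selection bias". Trial Design sets the rollout. In the first period "all of the patients scheduled for a surgery in all of the participating hospitals receive usual care (control phase"); one further hospital then switches in each period, in one direction only, until all nine have switched by period 10.

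Under Effect Evaluation, the adjusted Cox model for the primary outcome includes hospital as a random effect and "time period, to adjust for naturally occurring changes over time irrespective of the intervention". A time period by intervention term is optional. A footnote to Table 3 marks the process measures as "only intervention group".

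**The concern.** A reader will take the sentence on blind analysis as a safeguard against bias. It matters because the outcomes are self-reported by patients who know their arm, and because the plan leaves several analytic choices open:

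- which baseline differences are large enough to become covariates;
- whether an uneven spread of severe complications leads to adjustment;
- whether the interaction term is used;
- who counts as per protocol.

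Someone who can see the arms, and then the results by arm, could be influenced in these choices. If the analyst is not blind, the safeguard is absent and the choices need protection by other means.

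**Working it through.** The claim contains no figure to reproduce. The check is whether the variables that the analysis needs reveal the arm.

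**Inputs.** 9 hospitals and 10 periods (Sample Size). Number the hospitals i = 1 to 9 in their randomized order and the periods t = 1 to 10. By Trial Design, hospital 1 switches in period 2, hospital 2 in period 3, and so on.

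**Rule.** Hospital i delivers the intervention in period t if and only if t ≥ i + 1.

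**Both variables known.**
- Cells: 9 × 10 = 90.
- Intervention hospitals per period: 0, 1, 2, 3, 4, 5, 6, 7, 8, 9, which sum to 45.
- Control cells: 90 − 45 = 45.
- Each cell holds one arm only, so hospital plus period gives the arm for 90/90 = 100% of patients treated as scheduled.

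**One variable known**, with the rollout order also known and equal numbers per cell, as the sample size section assumes. The best guess is the commoner arm.
- Period only: 9 + 8 + 7 + 6 + 5 + 5 + 6 + 7 + 8 + 9 = 70 cells right, and 70/90 = 78%.
- Hospital only: 9 + 8 + 7 + 6 + 5 + 6 + 7 + 8 + 9 = 65 cells right, and 65/90 = 72%.

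**Arms and hospitals recoded, periods in order.** Whichever code is the only one present in period 1 is control, and whichever is the only one present in period 10 is intervention. The recoding is undone at once.

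**Period labels scrambled as well.** Put i' = 10 − i and t' = 11 − t. The condition t ≥ i + 1 becomes t' ≤ i', which is the control condition in the new labels. The layout is therefore unchanged by reversing time and swapping the arms, so full scrambling could in principle mask which arm is which. The plan describes no such step, and the optional interaction term, meant to capture an effect that grows with time since implementation, needs the true time order.

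**Which analyses need what (Effect Evaluation).**

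| Analysis | Hospital | Time period |
|---|---|---|
| Adjusted Cox, primary outcome | yes | yes |
| Crude Cox, primary outcome | no | no |
| Mixed models, secondary outcomes | yes | not listed |

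The full 100% result thus applies to the adjusted primary analysis.

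**Who knows the allocation already.** The research team tells patients their arm (Randomization) and issues the portal log-ins (eHealth Intervention). The principal researcher arranges each hospital's switch (Cluster Level). The article names no separate analyst.

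**The case against.** The strongest reply is that this is one misstated sentence with small consequences. The same section admits that researchers are not blinded, and Strengths and Limitations names lack of blinding as the first limitation. The article is condensed, so masking procedures may stand in a fuller document. That would answer an omission. It does not rescue a stated reason that does not support the claim.

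Several stronger readings are tempting, and the document does not support them.

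- *Analysis is the only protected step.* It is not. Randomization keeps the schedule from physicians until about a month before the switch, keeps the design from participants, has the research team do the counseling, and discloses allocation only after consent and the first questionnaire.
- *An unblinded analyst could steer the primary outcome through the recurrence rule.* The rule reads "The recurrence of sick leave due to the gynecologic surgery within the four week period after initial full RTW will be added" to the earlier spell. No section has an analyst or committee decide what is due to surgery. Return to work comes from calendars that patients complete, so attribution appears to be patient-reported. Masking the analyst would not change it.
- *Every analysis reveals the arm.* The crude Cox model needs neither variable, and the secondary models do not list time period.
- *Process data give the arm away.* They exist for one arm only, but nothing says that the portal logs or consultation records sit in the effect dataset.

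It is also fair to say that the loose analytic choices are cured by prespecification, whether or not the analyst is blind. Nor can everything be done without arm information. The plan picks covariates by comparing the arms, and applying a per-protocol rule would presumably need usage records. Both points stand and limit the fix.

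**Conclusion.** The claim of blind analysis is wrong as written and should be corrected. Hospital and ordered time period, both required by the adjusted primary Cox model, determine the arm of every patient treated as scheduled. A study code does nothing to hide this, and no other masking step is described.

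The result assumes that hospitals switched in the planned sequence and that the analyst sees the periods in order. A patient whose care departed from the schedule would be an exception.

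A reader might infer that the trial's result is biased. The document does not support that. It gives no figure from which a bias could be computed, and the form of the primary model and the subgroups are already stated. Any bias is probably modest, and smaller still if the open choices are settled in advance.

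**What to change.** 1. In Blinding, delete the claim that the analysis is blind because of study codes, and state that model fitting is unblinded.
2. Derive and clean the return-to-work outcomes on an extract that records time as days from surgery and leaves out hospital, surgery date, time period, arm and process data.
3. Before allocation is merged, fix in writing:
   - the covariate set, as prespecified prognostic factors and not factors chosen by observed differences between arms;
   - whether the time period by intervention term is used;
   - the per-protocol rule;
   - the analysis code.
4. Merge allocation, apply the per-protocol rule with whatever usage records it needs, and fit the models.

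The cost is slightly more data handling, mainly converting calendar dates to days from surgery, and revised wording in Blinding, Prognostic Factors and Effect Evaluation. The Results section says that cleaning and analysis had not begun at submission, so the sequence was still feasible. The fix does not touch patients' own attribution of sick leave, which remains unblinded.
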